### Study population

Patients are eligible for participation if they (1) are scheduled for laparoscopic colorectal surgery, (2) are aged > 18 years, (3) have an American Society of Anesthesiologists (ASA) physical status I to III, and (d) have no cognitive deficits. Exclusion criteria are (1) no written informed consent; (2) emergency or unplanned surgery; (3) pregnancy or breastfeeding; (4) immunologic or neuromuscular diseases; (5) advanced stage of cardiopulmonary, renal or hepatic disease; and (6) allergy to or contraindications for rocuronium or sugammadex.

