### Randomisation and blinding

Patients are randomised in a 1:1 ratio to an individualised pneumoperitoneum pressure strategy (the intervention group) or a standard pneumoperitoneum pressure strategy (the control group). Local investigators perform randomisation using a web-based automated randomisation system (Biostatistics Unit of the Health Research Institute La Fe, Valencia, Spain). Randomisation is performed with random block sizes and is stratified per centre. While attending anaesthesiologists are aware of the assigned pneumoperitoneum pressure strategy, the attending surgeons as well as the patients remain unaware of the assigned pneumoperitoneum pressure strategy at all times, i.e. before surgery, during surgery and after surgery. The PQRS is a patient-reported outcome (PRO), meaning that the investigator has little room to cause bias. The pneumoperitoneum insufflator screen is covered by a surgical drape. Study team members, who are not blinded to randomisation, perform postoperative PQRS measurements.

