### Individualised pneumoperitoneum pressure strategy

The multifaceted individualised pneumoperitoneum strategy consists of the following elements, which will be performed in the same order in all patients in the intervention group: (1) patient position is modified to increase the anteroposterior intra-abdominal space by correcting lumbar lordosis; (2) patients receive deep neuromuscular blockade throughout surgery to maintain a TOF of 0 and a post-tetanic count (PTC) between 1 and 5; (3) the abdominal wall and muscles are prestretched by maintaining an IAP of 15 mmHg for 5 min during the first CO_2_ gas insufflation and insertion of trocars (to achieve this, the CO_2_ gas insufflator will be initially set at 15 mmHg with a flow rate of 3 L∙min^− 1^); and (4) individualised IAP titration is used when the patient is placed in the surgical position (0–30° Trendelenburg); for this, the flow rate is increased to 30 L∙min^− 1^ and the IAP is decreased from 15 to 12 mmHg, and thereafter stepwise to 11, 10, 9 and finally 8 mmHg as long as the attending surgeon keeps an ‘adequate’ workspace. As in the standard pneumoperitoneum pressure group, surgeons can request an IAP increase up to 15 mmHg, which will be performed likewise. Of note, a pressure increment can be requested by the surgeon at all times in both study arms, where it always follows a similar approach; the previous feasibility study showed that an IAP increase was requested only one time in one-fifth of the patients and never twice [23].

Neuromuscular blockade pharmacological reversion at the end of surgery, before tracheal extubation, is achieved with sugammadex 4 mg∙kg^− 1^.

For clarity, the elements of the two group strategies are summarised in Table 1.

**Table 1 Tab1:** Intervention sequence

Standard pneumoperitoneum pressure strategy (SPP group)	Individualised pneumoperitoneum pressure strategy (IPP group)
1. Trendelenburg (0–30°) placement	1. Trendelenburg (0–30°) + ‘modified lithotomy position’, with flexed hips (between 45 and 90°) and legs raised in padded supports to increase anteroposterior intra-abdominal space
2. Moderate neuromuscular blockade throughout surgery (TOF between 2 and 4)	2. Deep neuromuscular blockade throughout surgery (TOF of 0 and a PTC between 1 and 5)

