### Secondary outcomes

Secondary outcomes include recovery of PQRS at 15 min (T15) and at 40 min (T40) after arrival in the post anaesthesia care unit (PACU) and in the surgical wards during the morning at postoperative day 3 (POD3). Other secondary clinical outcomes include daily postoperative complications until hospital discharge and at postoperative day 28, hospital length of stay (LOS) and secondary process-related outcomes that include the highest IAP level and IAV at which surgery could be performed, hepatic perfusion during pneumoperitoneum and the ventilatory parameters plateau pressure and driving pressure.

Occurrences of diaphragm and abdominal wall contractions or spontaneous breathing efforts and coughing during surgery are collected and compared between the two study groups.

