Grade II	Requiring pharmacological treatment with drugs other than such allowed for Grade I complications Blood transfusions and total parenteral nutrition are also included
Grade III	Requiring surgical, endoscopic or radiological intervention
- IIIa	Intervention not under general anaesthesia
- IIIb	Intervention under general anaesthesia
Grade IV	Life-threatening complication (including CNS complications)^a^ requiring IC/ICU management
- IVa	Single organ dysfunction (including dialysis)
- IVb	Multiorgan dysfunction
Grade V	Death of a patient
Suffix ’d’	If the patient suffers from a complication at the time of discharge, the suffix ’d’ (for ‘disability’) is added to the respective grade of complication. This label indicates the need for a follow-up to fully evaluate the complication

^a^Brain haemorrhage, ischaemic stroke, subarrachnoidal bleeding, but excluding transient ischaemic attacks (TIAs)

*IC* intermediate care, *ICU* intensive care unit, *CNS* central nervous system

Respiratory system driving pressure (ΔP_rs_) is calculated by subtracting positive end-expiratory pressure (PEEP) from Pressure plateau (Pplat) [34]. Perioperative safety issues are recorded during the surgery and are related to involuntary patient movements, and defined as diaphragm or abdominal wall contractions or spontaneous breathing efforts or coughing during anaesthesia.

Hospital LOS is defined as hospital discharge date minus hospital admission date.

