Differences in continuous variables between groups (IAP, IAV, LOS, inflammatory biomarkers) will be assessed by linear regression or with the Mann-Whitney *U* test (if the normal distribution assumption is rejected by the Shapiro-Wilks test). Differences in ΔP_rs_ between groups will be assessed by linear regression. A multivariable model introducing BMI, previous laparoscopic surgery and age will be fitted for predictive purposes.

Differences in the plasma disappearance rate of ICG are assessed by beta regression. Occurrences of cough or spontaneous movements during anaesthesia are assessed by logistic regression.

The relationship between IAP and IAV will analysed by linear interpolation from the individual IAP/IAV curves. The IAP before CO_2_ gas insufflation (IAP at volume zero) will be estimated by fitting multiadaptive linear regression splines to the IAV and IAP relationship. If a variable has a frequency of missing data > 5%, data will be imputed by the multiple imputation method.

As there is no ethically unacceptable risk related to the primary outcome analysed, there will be no planned interim analysis.

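### Length of stay is counted from admission, so the between-group test carries preoperative days that the intervention cannot affect: avoidable noise, not bias

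*Protocol article*

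**What the plan says.** In the protocol article, Definitions sets the rule in one sentence: "Hospital LOS is defined as hospital discharge date minus hospital admission date". The date of surgery plays no part in it.

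Secondary outcomes lists LOS among the secondary clinical outcomes, next to postoperative complications. Analysis plan names the test: "Differences in continuous variables between groups (IAP, IAV, LOS, inflammatory biomarkers) will be assessed by linear regression or with the Mann-Whitney" U test, the latter when normality is rejected.

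Three other statements bear on the point:

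- Surgery is scheduled only. Study population excludes "emergency or unplanned surgery".
- The strategy starts on the operating table. Its first element, in the section on the individualised strategy, is that "patient position is modified to increase the anteroposterior intra-abdominal space by correcting lumbar lordosis". Blockade, prestretching and pressure titration follow.
- On allocation, Randomisation and blinding says: "Randomisation is performed with random block sizes and is stratified per centre".

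**The concern.** A between-group test should measure time that the treatment can influence. Here the clock starts at admission, while the first element of the strategy comes with positioning for surgery. Time spent in hospital before that point reflects scheduling, preparation and local habit.

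The other recovery outcomes start at or after surgery: Post-operative Quality of Recovery Scale (PQRS) assessments at 15 and 40 minutes after arrival in the recovery unit and on postoperative days 1 and 3, and complications to postoperative day 28. LOS alone reaches back before treatment.

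At stake is precision. The Discussion names LOS with the PQRS and complications as what the study uses to examine recovery. It also concedes that the sample may be too small for some secondary outcomes. Adding variance unrelated to treatment makes that worse for no gain in the comparison.

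**Working it through.** **What the documents supply.** They give no mean, standard deviation, expected difference or preoperative stay for LOS, so there is no LOS figure of the plan to reproduce. They do give the sample size: 170 patients required (85 per arm) and 190 recruited (95 per arm). The two agree with the stated 10% dropout, since 170 / 0.90 = 188.9.

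**Direction.** Write total stay as preoperative stay plus postoperative stay. The expected difference between arms is then the difference in preoperative means plus the difference in postoperative means. Preoperative stay precedes treatment and allocation is 1:1 within centre, so the first part is zero in expectation. The estimate is not shifted; only its variance changes.

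**Size, under assumed values.** Let δ be the difference in mean stay, σ_post and σ_pre the standard deviations of postoperative and preoperative stay (taken as independent), and n = 85 per arm, with a two-sided 5% level:

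- σ_total = √(σ_post² + σ_pre²)
- power ≈ Φ( δ / (σ_total × √(2/n)) − 1.96 ), with √(2/85) = 0.1534

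Worked case: δ = 1 day, σ_post = 3 days, σ_pre = 1 day. Then σ_total = √10 = 3.162, the ratio is 1 / (3.162 × 0.1534) = 2.06, and Φ(0.10) gives 54.0%. With σ_pre = 0 the ratio is 1 / (3 × 0.1534) = 2.17, and power is 58.4%.

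| Assumed σ_post, δ (days) | σ_pre = 0 | 0.5 | 1 | 2 |
|---|---|---|---|---|
| 3, 1 | 58.4% | 57.3% | 54.0% | 44.0% |
| 5, 2 | 74.1% | 73.7% | 72.5% | 67.8% |
| 3, 2 | 99.1% | 99.0% | 98.5% | 95.1% |
| 5, 1 | 25.6% | 25.4% | 24.8% | 22.7% |

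In the first two rows, where power is neither near its ceiling nor very low, the loss is 0.4 to 1.1 points at σ_pre = 0.5, 1.6 to 4.4 points at 1, and 6.3 to 14.4 points at 2. In the last two rows it is smaller: 0.1 to 0.8 points up to σ_pre = 1, and 2.9 to 4.0 points at 2.

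**Skewed stays.** The formula compares means, whereas LOS may well go to the Mann-Whitney test. A simulation with log-normal postoperative stays (medians 5 and 4.15 days, log-SD 0.45, 95 per arm, 4,000 replicates per scenario) gave 78 to 79% power without preoperative days. Power was 76% with 0 or 1 day equally likely, 72% with 0, 1 or 2 days equally likely, and 71% with mostly 1 day and 5% of patients at 5 days. All these inputs are assumed, and 95 per arm is the number before dropout. The direction and rough size agree with the table.

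**Limiting case.** If every patient has the same preoperative stay, including none, σ_pre = 0. Differences in means and ranks are then the same on either clock.

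**The case against.** The strongest reply is that admission to discharge is simply what hospital length of stay means. The definition is explicit and reproducible, contradicts nothing else in the article, and measures bed use, which matters in its own right. Postoperative stay is a different quantity. Allocation is balanced, so nothing is biased. Enhanced recovery care is suggested at all sites, and with same-day admission the issue disappears. The trial was not powered for LOS, and every figure for the loss rests on assumptions.

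Most of this stands. Total stay is a legitimate quantity to report, the comparison is unbiased, and the loss may be nil. That preoperative stay differs between centres is a possibility, not something the article shows. None of it is a reason to prefer the noisier clock for the treatment comparison, and low power for secondary outcomes argues for removing noise, not for tolerating it.

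A reader might also infer that a patient who dies in hospital would be credited with a short, favourable stay. The article does not support that. It never equates death with discharge, and it records death separately as Clavien-Dindo Grade V. How deaths enter the LOS analysis is commonly left to the statistical analysis plan, which is not shown. Silence on this in an article is not a defect.

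**Conclusion.** The point holds as one of precision. As defined, LOS includes any preoperative days in a between-group test of an intervention that begins in the operating room. A reader might go further and infer a systematic tilt towards one arm; randomisation within centre rules that out in expectation.

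The cost is roughly 0.4 to 4 points of power for a preoperative standard deviation of 0.5 to 1 day, and about 6 to 14 points at 2 days. This assumes 85 per arm, the postoperative spreads and effects in the first two rows of the table, and independence of preoperative and postoperative stay. It is zero if preoperative stay does not vary. No document figure fixes where in this range the trial lies. This is a desirable refinement to a secondary outcome; the primary outcome, significance level and sample size are unaffected.

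**What to change.** For the between-group test, define postoperative LOS as discharge date minus date of surgery. Keep total stay from admission as a descriptive item by arm.

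The change is about one line in Definitions and needs no new data, because the trial must already hold the surgery date to count postoperative days 1, 3 and 28. There are two modest costs. The tested figure is no longer total bed-days, which is why total stay should still be reported. It also alters a stated secondary outcome in a trial that has been recruiting since February 2017, so it should be documented with its date and made before any comparison of outcomes by arm. If the sponsor prefers to leave the stated definition untouched, postoperative LOS can be added beside it, with a statement of which of the two carries the formal comparison.

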### Data to be collected

Before anaesthesia demographic data will be collected including age (years), gender, body height (centimetres) and body weight (kilograms), BMI (kilograms per metre squared), ASA physical status score, comorbidities, number of previous abdominal surgeries and number of previous laparoscopic surgeries and PQRS score.

During anaesthesia the following data will be obtained: levels of IAPs at which surgery is performed (mmHg) in both groups; proportion of patients who needed a pressure increment to achieve acceptable surgical workspace; IAV at start of pneumoperitoneum (litres); coughing and spontaneous movements (yes/no); type of surgery and oncologic status; duration of surgery (minutes); duration of anaesthesia (minutes); proportion of patients who needed conversion from laparoscopic to open surgery and the reason for it (only if applicable); ventilation data including PEEP, plateau pressure and respiratory driving pressure (ΔP_rs_) (all in centimetres of H_2_O pressure) before pneumoperitoneum generation and during initial IAP titration until a stable level of IAP is reached in both groups; type and dose of neuromuscular blocking agent (milligrams); type and dose of neuromuscular blocking reversal agent (milligrams); total opioid requirement during the first 24 h if used (milligrams); and PDR_ICG_ in the stable pneumoperitoneum phase.

Directly after anaesthesia, in the PACU the following will be obtained: PQRS score at 15 and 40 min after PACU admission and on POD1 and POD3; PQRS score in the morning and peripheral venous blood samples for determination levels of biomarkers.

On all postoperative days until hospital discharge and at day 28 the occurrence of postoperative complications and location will be noted.

### Analysis plan

The statistical analysis plan (SAP) is specified before enrolment of the first patient. In the absence of studies assessing differences in recovery, based on intraoperative IAP management during laparoscopic colorectal surgery, we performed the sample size calculation assuming an odds ratio of 2.65 (equivalent to a difference of 0.5 unit in the logit scale) between groups in the recovery of physiologic PQRS score. It was estimated that a sample size of 170 patients is required to achieve 80% power at a significance level of alpha = 0.05. All reasons for dropouts, expected to be as low as 10%, will be collected and reported. Conversion to open surgery was the main reason for dropouts in the previous study. We will recruit a total of 190 patients to compensate for potential losses.

All analyses will be performed with R software (R Foundation for Statistical Computing, Vienna, Austria). Data will be expressed as the mean (standard deviation, SD) or median (interquartile range, IQR) for continuous variables depending on their distribution (normality will be checked with the Shapiro-Wilks test) and by counts and proportions for categorical variables. The 95% confidence intervals will be calculated for each of the estimated percentiles. The statistical significance level will be set at *P* < 0.05.

The analysis of the primary endpoint follows the intention-to-treat principle. The difference between the recovery PQRS score between groups, the primary outcome on POD1, will be assessed by mixed ordinal logistic regression introducing the patient as random factor, and age, weight, BMI and sex as covariables. The differences in Clavien-Dindo grading of postoperative complications will be assessed by ordinal regression.

For IAV calculation the relationship between IAP and the insufflated volume of CO_2_ will be determined for each patient during initial pneumoperitoneum insufflation. The relationship between IAP and IAV was analysed by linear interpolation from the individual IAP/IAV curves to determine the actual IAV at which surgery is performed. The IAP before CO_2_ gas insufflation was considered the basal IAP or IAP at volume zero, and it was estimated by fitting multiadaptive linear regression splines to the IAV and IAP relationship.

Differences in continuous variables between groups (IAP, IAV, LOS, inflammatory biomarkers) will be assessed by linear regression or with the Mann-Whitney *U* test (if the normal distribution assumption is rejected by the Shapiro-Wilks test). Differences in ΔP_rs_ between groups will be assessed by linear regression. A multivariable model introducing BMI, previous laparoscopic surgery and age will be fitted for predictive purposes.

Differences in the plasma disappearance rate of ICG are assessed by beta regression. Occurrences of cough or spontaneous movements during anaesthesia are assessed by logistic regression.

The relationship between IAP and IAV will analysed by linear interpolation from the individual IAP/IAV curves. The IAP before CO_2_ gas insufflation (IAP at volume zero) will be estimated by fitting multiadaptive linear regression splines to the IAV and IAP relationship. If a variable has a frequency of missing data > 5%, data will be imputed by the multiple imputation method.

As there is no ethically unacceptable risk related to the primary outcome analysed, there will be no planned interim analysis.

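### The sample size rests on one effect given as two incompatible values: an odds ratio of 2.65 is 0.97 on the logit scale, and 0.5 logit is an odds ratio of 1.65

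*Protocol article*

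**What the plan says.** The protocol article gives one effect assumption, in the Analysis plan section, for recovery of the physiologic PQRS score: "assuming an odds ratio of 2.65 (equivalent to a difference of 0.5 unit in the logit scale) between groups". From it the article derives that "a sample size of 170 patients is required to achieve 80% power at a significance level of alpha = 0.05". On losses it says "All reasons for dropouts, expected to be as low as 10%, will be collected and reported", and then "We will recruit a total of 190 patients to compensate for potential losses". The significance threshold appears again in the same section ("The statistical significance level will be set at *P* < 0.05"), without saying whether the test is one- or two-sided. Under Randomisation and blinding, "Patients are randomised in a 1:1 ratio", so 170 patients means 85 per arm.

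The section on the PQRS defines recovery as a yes/no outcome at each time point. The Analysis plan names a mixed ordinal logistic model with a random patient factor for the day-1 comparison. Nothing else in the article restates, corrects or explains the effect size.

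**The concern.** A logit difference is the logarithm of an odds ratio, so either number fixes the other. The two printed here do not match, and they differ almost twofold on the log-odds scale. Both numbers and the claim that they are equivalent stand in one intact sentence, so this is neither a gap in the text nor a detail left to a fuller document.

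That sentence is the only stated basis for 170 patients and 80% power, and the Discussion presents the sample size as a strength. If 0.5 logit was the planning effect, the power claim is wrong by a wide margin. If 2.65 was, the power claim can stand, but the parenthesis tells readers that the trial can detect an effect about half as large on the log-odds scale as the one it was sized for. Either way, a reader cannot tell which effects a non-significant result would speak against.

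**Working it through.** **Inputs.** From the Analysis plan: OR 2.65, logit difference 0.5, N = 170, power 80%, alpha 0.05, dropout 10%, recruitment 190. From Randomisation and blinding: 1:1 allocation, so n = 85 per arm. Assumed here: a two-sided test, 170 evaluable patients, one day-1 observation per patient, and a range of control recovery rates, because the article gives none.

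**Step 1: the conversion.** ln(2.65) = 0.975 and exp(0.5) = 1.649. The ratio on the logit scale is 0.975 / 0.5 = 1.95. This step needs no assumption.

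**Step 2: recruitment.** 170 / 0.9 = 188.9, so 190 is consistent with 170.

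**Step 3: can 170 be reproduced from OR 2.65?** With control rate p1, the intervention rate is p2 = OR·p1 / (1 − p1 + OR·p1). With m the mean of p1 and p2, the size per arm is

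n = [1.960·√(2m(1−m)) + 0.842·√(p1(1−p1) + p2(1−p2))]² / (p2 − p1)².

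Example at p1 = 0.20: p2 = 0.53 / 1.33 = 0.398 and m = 0.299, so n = (1.269 + 0.532)² / 0.1985² = 82.4. That rounds up to 83 per arm, or N = 166.

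Without continuity correction, N is about 170 at control rates of about 19% and 62%. With it, N is 170 at 24%, 168 at 25% and at 54%, and 172 at 55%. So 170 can be reached from OR 2.65 at several ordinary control rates.

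**Step 4: power of 85 per arm, binary recovery.** Power = Φ{[|p2 − p1|·√85 − 1.960·√(2m(1−m))] / √(p1(1−p1) + p2(1−p2))}. N below is without continuity correction.

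| Control rate | Power, OR 2.65 | N for 80%, OR 2.65 | Power, 0.5 logit | N for 80%, 0.5 logit |
|---|---|---|---|---|
| 20% | 81% | 166 | 28% | 688 |
| 30% | 87% | 140 | 34% | 552 |
| 40% | 88% | 136 | 37% | 510 |
| 50% | 86% | 144 | 36% | 514 |
| 60% | 81% | 166 | 34% | 562 |
| 70% | 72% | 206 | 29% | 674 |
| 80% | 56% | 296 | 22% | 928 |

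Over all control rates, the best power for 0.5 logit is 36.6% (control rate about 44%), and the smallest N for 80% is 506.

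**Step 5: the most favourable ordinal case.** Whitehead's proportional-odds formula is N = 12(1.960 + 0.842)² / [θ²(1 − Σp³)], where the p are the mean category proportions. Power is Φ{θ·√[N(1 − Σp³)/12] − 1.960}. For θ = 0.5 with equal categories:

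- three levels: N = 424, power at 170 = 42.6%
- five levels: N = 392, power at 170 = 45.4%
- limit of many levels: N = 12 × 7.849 / 0.25 = 377, power = Φ(0.5·√(170/12) − 1.960) = Φ(−0.078) = 46.9%

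A simulated rank test on continuous logistic data (10,000 runs, 85 per arm) gave 46.4%, in agreement with the limit.

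**Step 6: how far the assumptions matter for 0.5 logit.** With a one-sided 5% test the ceilings become 49% (binary) and 59% (ordinal limit). With all 190 patients analysed, two-sided, they become 40% and 51%. All remain well below 80%.

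**Step 7: smallest OR detectable with 80% power at 170.** Binary: 2.61, 2.42, 2.38, 2.43 and 2.60 at control rates of 20, 30, 40, 50 and 60%. Ordinal, exp{2.802·√(12 / [170(1 − Σp³)])}: 2.20 with three equal levels, 2.14 with five, 2.11 at the limit.

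**The case against.** The strongest reply is that this is only a wrong conversion in a parenthesis. OR 2.65 with 170 patients gives the stated power or more over a broad range of control rates. No binary or single-observation ordinal calculation brings 0.5 logit near 170. That stands as the more likely reading, but the article does not settle it: since exp(0.5) is 1.65, 2.65 could equally be a misprint for 1.65, and then the power claim fails.

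A second reply is that a random patient factor implies several observations per patient, which adds power. This stands as a limit on the 37% and 47% figures. With four observations per patient and an assumed within-patient correlation of 0.1 to 0.5, power for 0.5 logit would be roughly 54 to 82% (binary) or 66 to 91% (ordinal limit). But the article describes no such sizing and its primary contrast is day 1 alone. Nor would pooling make 2.65 equal to 0.5 logit.

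A reader might also infer that the absent control recovery rate is itself a defect, or that 170 can arise from OR 2.65 only at rates near 19% or 62%. Neither is supported. A condensed article commonly leaves the rate and the formula to the full protocol or analysis plan, and the continuity-corrected formula reaches about 170 at 24 to 25% and 54 to 55%.

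**Conclusion.** The sentence is wrong as written. That part is plain arithmetic and rests on no assumption. The size of the consequence depends on which figure was used:

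- **OR 2.65 used:** the 80% claim can hold (81 to 88% for binary recovery at assumed control rates of 20 to 60%; 72% at 70% and 56% at 80%). The fault is that the planned effect is understated by about half on the log-odds scale.
- **0.5 logit used:** the 80% claim fails, on the assumptions of a two-sided 5% test, 170 evaluable patients and one day-1 observation each.

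A reader might go further and conclude that the trial is undersized, or that its power cannot exceed 47%. The article does not support either. The first requires that 0.5 logit was the planning effect, which is not shown and fits 170 less well. The second holds only under the conditions just listed. Nor would a null result be empty, since its confidence interval could still exclude large effects.

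**What to change.** State which effect was used for the calculation and correct the other figure.

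- If it was OR 2.65, replace 0.5 unit with 0.97 unit.
- If it was 0.5 logit, replace 2.65 with 1.65 and restate the power at 170 evaluable patients under the planned model.
- In either case, report the smallest odds ratio detectable with 80% power at 170 under the authors' own model and assumptions. For orientation only, this is about 2.4 to 2.6 for a binary endpoint at control rates of 20 to 60%, and about 2.1 to 2.2 for an ordinal outcome with three or more equal levels. These figures should not be copied in unless they match the model actually planned.

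Enrolment and conduct do not change. The cost is a few words and a stated power or detectable effect that looks less favourable than the present text.
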